### Study design

2.2.

#### Long-term effects of RLI on acetabular development after closed reduction of DDH: a multicenter retrospective cohort study

2.2.1.

We retrospectively analyzed the outcomes of RLI as well as the mid- and long-term impact of RLI on acetabular development in DDH patients receiving closed reduction at different centers. The trail is illustrated in a flowchart as shown in Figure 2.

**Figure 2 F2:**
[figure not shown]
Flow diagram of the multicenter retrospective cohort study.

##### Inclusion criteria

2.2.1.1.

1.Pediatric patients undergoing closed reduction at 6–18 months of age;2.No other treatment prior to DDH reduction, with or without the administration of pre-reduction traction or percutaneous adductor tenotomy;3.After DDH reduction, a Spica cast was applied to immobilize the hips in ≤65° of abduction for 3 months, followed by use of abduction braces for 3 months;4.Patients must have a successful closed reduction, defined as a stable reduction enabling femoral head-acetabulum concentricity as suggested by frontal pelvic radiographs taken at 9–12 months after DDH reduction;5.Follow-up for more than 5 years.

##### Exclusion criteria

2.2.1.2.

1.Neuromuscular or syndromic DDH;2.Repeated surgical treatment because of re-dislocation, RAD, or other reason after DDH reduction;3.Incomplete imaging data.

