## Abstract

Closed reduction is a common treatment method for developmental dysplasia of the hip (DDH) in children aged 6–18 months. Residual acetabular dysplasia (RAD) is the most common complication associated with closed reduction. Residual limbus inversion (RLI) is a common condition following DDH closed reduction. Previously, we confirmed that when limbus inversion exceeds 32.2% of the acetabular depth after closed reduction, RLI persists and leads to RAD; however, this was based on a small cohort with a short-term follow-up period. The long-term fate of RLI and the correlation between RLI and RAD have yet to be verified. Therefore, this multicenter clinical study protocol was designed in three parts to investigate the effect of RLI on acetabular development after closed reduction of DDH (a multicenter retrospective cohort study), effect of RLI clearance on acetabular development (a multicenter retrospective and prospective randomized controlled study), and influence of inverted limbus clearance on acetabular development during DDH reduction (a multicenter prospective cohort study). Statistical analysis was performed by assessing the basic measures of acetabular development including the acetabular index and central-edge angle using frontal pelvic radiographs; the magnitude of limbus inversion, cartilaginous acetabular index, and T1ρ mapping values were measured using magnetic resonance imaging. The multicenter retrospective cohort studies required 5 years of follow-up period at minimum, and the prospective randomized controlled studies required reviews of frontal pelvic radiographs every 6 months as well as data pooling every 2 years to compare the short- and mid-term outcomes of hip joint morphological development between the two groups of pediatric patients. This research program is expected to verify that RLI following closed reduction of DDH can affect acetabular development and that limbus excision during DDH reduction can improve postoperative RAD. Therefore, the indication and timing of surgical intervention for RLI after closed reduction of DDH provide a basis for revising the acceptable criteria for utilizing closed reduction of DDH to reduce the incidence of osteoarthritis caused by RAD following DDH treatment.

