##### Statistical analysis

2.2.1.4.

Statistical analysis was performed using SPSS 27.0 software (IBM, SPSS Inc.).
1.To ensure consistency and reliability between multicenter research samples, it is first necessary to conduct a consistency analysis on the structural data, such as age and sex, of the included cases from each center and the International Hip Dysplasia Institute (IHDI) classification using the Cohen's kappa statistic. Simultaneously, the baseline characteristics (such as structural composition and pathological severity) of the included cohorts within each center must be consistent; imbalances in baseline characteristics were corrected by increasing the sample size.2.The included patients were divided into the non-limbus inversion group (A) and the limbus inversion group based on the presence of limbus inversion at closed reduction. The limbus inversion group was then further divided into the RLI group (B) and the resolved inverted limbus group (C) according to the state at final follow-up. A combination consisting of any two of the groups was organized into cohorts. Fisher's precision probability test was used to compare the difference between the sexes and affected sides, using analysis of variance to compare the different ages between the two groups. Differences in acetabular index was compared using Student's *t*-test. Chi-square test was used to compare IHDI classification, VAS and HHS, and Severin classification at the final follow-up, and analysis of variance was used to compare the MRI T1ρ mapping values and the difference in the initial magnitude of limbus inversion between groups B and C, as well as the difference between the initial magnitude of limbus inversion and that at the final follow-up in group B.3.ROC curve analysis was used to predict the cut-off value of the initial magnitude of limbus inversion in the case of persistent RLI as well as calculate its specificity, sensitivity, and statistical significance.4.Sample size calculation.In this study, ossification of the acetabular cartilage was the main observation; thus, improvement of the acetabular index was the most suitable observation indicator. The sample size calculation was based on the previously published acetabular index at the final follow-up in the group with RLI and the group without RLI after closed reduction (21.41°±3.61° and 18.88 ° ± 4.32° in the two groups, respectively) (15). The significance level *α*, the statistical power of the test, the ratio of the sample sizes in the two groups, and the percentage of patients lost to follow-up were set at 0.05, 0.9, 1:1, and 20%, respectively. The minimum sample size for each group was calculated to be 67 cases (134 cases in total). Therefore, at least 67 cases needed to be enrolled in the observation group and the control group, respectively.

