###### Exclusion criteria

2.2.2.1.2.

Exclusion criteria 1–3 are the same as previously listed exclusion criteria 1–3 (2.2.1.2);
4. Patients who refused inclusion in the study cohorts.For pediatric patients satisfying the inclusion/exclusion criteria, the basic measures of acetabular development including the acetabular index and central-edge angle were assessed using frontal pelvic radiographs; the magnitude of limbus inversion, cartilaginous acetabular index, and T1ρ mapping values were measured using MRI.

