##### Research object

2.2.3.1.

In each center, the quality of reduction was first evaluated intraoperatively based on our published “safety and stability” criteria for an acceptable closed reduction (15), i.e., the safe zone >30° during intraoperative inspection and the reduction maintained with the hip in <65° abduction. DDH patients undergoing closed reduction at 6–18 months who satisfied the criteria were selected as participants for observation. The exclusion criteria are the same as those specified in study protocol 2.2.1. In the case of <70° abduction before DDH reduction, percutaneous adductor longus tenotomy was performed. The trail is illustrated in a flowchart as shown in Figure 6.

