##### Statistical analysis

2.2.3.4.

Fisher's precision probability test was used to compare the difference between the sexes and affected sides, using analysis of variance to compare the different ages between the surgical and non-surgical cohorts. Differences in acetabular index was compared using Student's *t*-test. The chi-square test was used to compare IHDI classification, VAS and HHS, and Severin classification at the final follow-up, and analysis of variance was used to compare the MRI T1ρ mapping values, re-dislocation rate, incidence of RAD, and incidence of AVN between the two cohorts.

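### Excluding children re-operated for RAD selects on the outcome in part 1, and the same exclusion, carried over unchanged, conflicts with the part 3 endpoints and has no time limit in part 2

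*Protocol article*

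**What the plan says.** Section 2.2.1.2 (part 1, retrospective cohort) excludes children with "Repeated surgical treatment because of re-dislocation, RAD, or other reason after DDH reduction". Inclusion criterion 5 in section 2.2.1.1 requires more than 5 years of follow-up, so this surgery can fall anywhere in a long window. The Abstract gives the motive for the programme: "The long-term fate of RLI and the correlation between RLI and RAD have yet to be verified". The sample size paragraph of section 2.2.1.4 says that "improvement of the acetabular index was the most suitable observation indicator" and takes as inputs "21.41°±3.61° and 18.88 ° ± 4.32° in the two groups, respectively" (RLI and no RLI); alpha, power, allocation ratio and loss to follow-up "were set at 0.05, 0.9, 1:1, and 20%, respectively".

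The other two parts take the criterion over by cross-reference:

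- Part 2, section 2.2.2.1.2: "Exclusion criteria 1–3 are the same as previously listed exclusion criteria 1–3 (2.2.1.2".
- Part 3, section 2.2.3.1: "The exclusion criteria are the same as those specified in study protocol 2.2.1". Section 2.2.3.4 then plans to compare "re-dislocation rate, incidence of RAD, and incidence of AVN between the two cohorts".

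The article does not say at what time the criterion applies in parts 2 and 3, or how a child re-operated after enrolment is counted.

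**The concern.** In part 1, eligibility depends on an event that happens after reduction and is brought about by the outcome. A child whose RAD was bad enough to be operated on is left out of the cohort meant to show whether RLI causes RAD. The plan itself indicates that this happens. The Introduction describes residual inverted limbus confirmed at surgery to correct RAD, and inclusion criterion 9 in section 2.2.2.1.1 says that an acetabular index above 30° usually leads to pelvic osteotomy. If RLI worsens acetabular development, more RLI than non-RLI hips are lost and the remaining difference is too small.

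In part 3 the criterion and the endpoints do not fit together. Children are selected at the reduction, so nobody can yet have had repeat surgery after it. If the criterion acts at all, it acts after enrolment, and it then deletes children who have the events that section 2.2.3.4 compares. In part 2, a criterion without a time limit could remove randomised children who need later surgery. Read literally, its words on other reasons would even cover the randomised arthrotomy.

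**Working it through.** **1. The plan's sample size (section 2.2.1.4).** Inputs: means 21.41° and 18.88°, SDs 3.61° and 4.32°, alpha 0.05 (sidedness not stated; two-sided reproduces the figure), power 0.9, ratio 1:1, loss 20%.

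- Difference: 21.41 − 18.88 = 2.53°.
- Common SD: √[(3.61² + 4.32²)/2] = 3.98°.
- n per group = 2 × [(1.960 + 1.282) × 3.98/2.53]² = 52.03, rounded up to 53.
- With loss: 53/(1 − 0.20) = 66.25, rounded up to 67.

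The stated 67 per group (134 in total) is reproduced.

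**2. Effect of the exclusion on the part 1 difference.** Assumptions: the acetabular index is normal in each group with the stated mean m and SD s, and every hip above a threshold c is re-operated and excluded. The thresholds are assumed. Only 30° is linked to surgery in the text, and there for children aged 5 years or less. With a = (c − m)/s, the share lost is 1 − Φ(a) and the mean of those remaining is m − s × φ(a)/Φ(a).

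| Threshold c | RLI hips lost | Non-RLI hips lost | Mean, RLI | Mean, non-RLI | Difference | Change from 2.53° |
|---|---|---|---|---|---|---|
| 30° | 0.9% | 0.5% | 21.32° | 18.82° | 2.51° | −1% |
| 25° | 16.0% | 7.8% | 20.36° | 18.19° | 2.17° | −14% |
| 23° | 33.0% | 17.0% | 19.46° | 17.56° | 1.90° | −25% |

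Example at 25°: a = (25 − 21.41)/3.61 = 0.994 for RLI, so the remaining mean is 21.41 − 3.61 × 0.2897 = 20.36°. For non-RLI, a = (25 − 18.88)/4.32 = 1.417 and the remaining mean is 18.88 − 4.32 × 0.1587 = 18.19°.

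At each threshold the RLI group loses roughly twice the share that the non-RLI group loses. If only half of the hips above 25° are re-operated, the difference is 2.38°; if a quarter, 2.46°.

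The SD shrinks along with the difference. At the three thresholds, power with 53 per group is 0.91 to 0.92. The harm is bias, not loss of power.

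**3. Effect on RAD in part 3, if the criterion acts after enrolment.** With true incidence p and a share q of RAD cases re-operated and dropped, the observed incidence is p(1 − q)/(1 − pq). The Introduction gives 11% and 38% as RAD figures after closed reduction; q is not given and is assumed.

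| True p | q = 25% | q = 50% | q = 75% | q = 100% |
|---|---|---|---|---|
| 11% | 8.5% | 5.8% | 3.0% | 0% |
| 38% | 31.5% | 23.5% | 13.3% | 0% |

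Example: 0.11 × 0.5/(1 − 0.055) = 5.8%. RAD is depleted, and disappears only if every case is re-operated. Re-dislocation is more exposed, because the Discussion calls closed reduction a surgical procedure, so a repeat reduction would count as repeat surgery.

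**The case against.** The best defence of the criterion is that later surgery changes the final acetabular index, Severin class and limbus state, so leaving these children out keeps the final measurements free of the operation. That is a fair reason not to use post-operative measurements. It is no reason to drop the child, whose course before surgery is known.

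For part 3, it can be said that the cross-reference stands in a section on selecting participants and, read as an entry rule, excludes nobody. The planned comparison of re-dislocation and RAD supports that reading. So does part 2, where applying the criterion after enrolment would remove the whole surgery arm. This stands in part: harm in part 3 is conditional. What remains is a criterion that is empty on one reading and contradicts the endpoints on the other.

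Some stronger inferences are tempting but not supported:

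- **That the RAD endpoint in part 3 is emptied and both cohorts look safe by construction.** RAD without repeat surgery is still counted, AVN is not targeted by the criterion, and post-enrolment use is not established.
- **That the ROC cut-off reused in parts 2 and 3 is distorted.** The ROC predicts persistent RLI from the initial inversion. Bias would need re-operation to depend on initial inversion beyond RLI status, which is not shown.
- **That the criterion duplicates inclusion criterion 2.** That criterion concerns treatment before reduction; this one concerns surgery after it.
- **That lost re-dislocations matter much in part 1.** Inclusion criterion 4 already requires a stable, concentric hip at 9–12 months, and no re-dislocation comparison is listed there.
- **That a bias of 14% or 25% is expected.** Those figures rest on assumed thresholds. At 30° the change is about 1%. The article also does not say whether the published means come from a cohort already selected in this way, in which case the illustration truncates twice.

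**Conclusion.** The point holds. In part 1 the stated rule selects on a consequence of the outcome. If RLI raises the acetabular index, the bias is towards no effect. Its size cannot be fixed from the document: between 2.51° and 1.90° against 2.53° over assumed thresholds of 30° to 23° with complete removal, and less if only some of those hips are re-operated. The sample size of 67 per group is not affected. In part 3 the inherited criterion must be reconciled with the endpoints, since it is either void or, applied after enrolment, removes re-operated re-dislocations and lowers the observed RAD incidence. In part 2 the gap is the missing time limit. Confidence is high on the part 1 selection and on the need to reconcile part 3, and low on any particular size.

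**What to change.** **Part 1.** Take surgery for RAD out of exclusion 2 and keep these children. Count secondary surgery for RAD as RAD = yes. Classify limbus state (groups B and C are otherwise set at final follow-up) from the last imaging or the operative finding before that surgery. Use the last acetabular index before surgery, and adjust for age or follow-up time, because these values are taken earlier than those of other children and the index changes with growth. Report the analysis that excludes re-operated children as a sensitivity analysis.

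**Part 2.** Limit exclusion 2 to surgery before randomisation, and state that children operated on later stay in the analysis.

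**Part 3.** State that repeat surgery after enrolment is an outcome and not an exclusion.

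**Cost.** Rewording in three sections and a chart search for re-operated children in part 1. Some of them will lack a late MRI and contribute radiographic data only. The sample size need not change.

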Magnetic resonance imaging (MRI) can display all bone and non-bone structures of the hip joint from multiple planes; therefore, it is useful for observing development of the acetabulum after closed reduction of DDH. However, MRI is commonly used to evaluate the pathological morphology of DDH before reduction and is seldom used for long-term follow-up (13, 14). In 2020, we published prospective MRI long-term follow-up results after closed reduction of DDH and established that “safety” (a reduction which could be maintained by the abduction of <65°) and “stability” (Ramsey safe zone >30°) are acceptable closed reduction standards (15). Owing to shaping of the pathological structure of soft tissue after reduction, non-concentric reduction of the DDH can gradually achieve concentric reduction. Additionally, we found an interesting phenomenon during follow-up using serial MRI: the inverted limbus was not absorbed overtime; instead, it was compressed into a thin layer of fibrous tissue inter-positioning in the superior joint space (15). Previous radiographic studies have shown that the inverted limbus can be absorbed and can disappear with gradual “docking” of the femoral head after reduction, but this is not the case. Intraoperative arthrography has shown that the inverted limbus is a hypertrophic filling defect with a widening superior joint space (Figure 1A); although this cannot be observed during the course of medium-term follow-ups (Figure 1B), MRI can reveal the residual inverted limbus as a thin layer of hypointense tissue embedded in the superior joint space (Figure 1C), as confirmed during surgery correcting for RAD (Figure 1D). This phenomenon has not been reported previously.

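### Part 1 is meant to verify the team's own small-cohort result, but its eligibility rules do not keep out that cohort's children, so the confirmation may rest partly on the data that suggested it

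*Protocol article*

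**What the plan says.** The Abstract reports the earlier result as established: "Previously, we confirmed that when limbus inversion exceeds 32.2% of the acetabular depth after closed reduction, RLI persists and leads to RAD". It then qualifies it, "however, this was based on a small cohort with a short-term follow-up period", and gives the reason for the new program: "The long-term fate of RLI and the correlation between RLI and RAD have yet to be verified".

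Part 1 addresses this retrospectively. The inclusion list (2.2.1.1) has five items, among them "Pediatric patients undergoing closed reduction at 6–18 months of age" and "Follow-up for more than 5 years". It sets no calendar dates and does not restrict where the children come from. The exclusion list (2.2.1.2) has three items, of which the last two read "Repeated surgical treatment because of re-dislocation, RAD, or other reason after DDH reduction;3.Incomplete imaging data". Membership of an earlier published cohort appears in neither list.

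Two analyses in 2.2.1.4 bear on the earlier result:

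- The acetabular-index comparison. "The sample size calculation was based on the previously published acetabular index at the final follow-up", namely 21.41 (SD 3.61) with RLI and 18.88 (SD 4.32) without. These values are cited to the same reference that the Introduction describes as the team's own MRI follow-up study.
- The ROC analysis, which estimates a cut-off of initial limbus inversion for persistent RLI. That value may replace 32% for entry to part 2 (2.2.2.1.1, item 8) and for cohort membership in part 3 (2.2.3.2).

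**The concern.** Verification needs data that did not generate the hypothesis. The earlier children had closed reduction for the same condition and were followed by MRI. The team that published them leads the new program (Discussion). Part 1 looks back in time, needs more than 5 years of follow-up, excludes incomplete imaging and uses MRI to establish RLI. The Introduction remarks that "MRI is commonly used to evaluate the pathological morphology of DDH before reduction and is seldom used for long-term follow-up", so children already followed by MRI are plausible candidates to meet the imaging requirement.

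If some of them enter, two things follow. The acetabular-index difference is pulled towards the published one whatever the new children show. The re-estimated cut-off is pulled towards 32.2%, so agreement between old and new values looks more like confirmation than it is. The second effect carries forward, because the Part 1 cut-off may decide who enters the randomised part and how the part 3 cohorts are formed.

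**Working it through.** **Inputs.** From 2.2.1.4: means 21.41 and 18.88, SDs 3.61 and 4.32, alpha 0.05, power 0.9, ratio 1:1, loss 20%, and 67 per group. Assumed, because the documents do not give it: the fraction f of each group that comes from the earlier cohort.

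**Step 1: reproduce the plan's figure.**

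- Difference = 21.41 − 18.88 = 2.53 degrees.
- Pooled SD = √((3.61² + 4.32²)/2) = 3.981.
- n per group = 2 × (1.960 + 1.282)² × 3.981² / 2.53² = 52.03, rounded up to 53 (two-sided).
- Allowing for loss: 53/0.8 = 66.25, rounded up to 67, or 134 in total.

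The stated figure reproduces exactly, so no number in the plan is wrong.

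**Step 2: number analysed.** 67 × 0.8 = 53.6, taken as 54 evaluable per group. The standard error of the difference is 3.981 × √(2/54) = 0.766. Two-sided significance needs an estimate beyond 1.96 × 0.766 = 1.50 degrees.

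**Step 3: effect of overlap when new children show no difference.** Let a fraction f of each group carry over with exactly the published 2.53 degrees.

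- Expected pooled estimate = f × 2.53.
- Remaining random error, from new children only = 0.766 × √(1 − f).
- Chance of significance = P(Z > (1.50 − 2.53f) / (0.766√(1 − f))) plus the small opposite tail.

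| Assumed overlap f | Shift (degrees) | Chance of a significant result |
|---|---|---|
| 10% | 0.25 | 5.1% |
| 20% | 0.51 | 7.5% |
| 30% | 0.76 | 12.4% |
| 40% | 1.01 | 20.5% |

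With the t critical value (1.98) in place of 1.96, the last column becomes 4.8%, 7.1%, 11.8% and 19.7%. Rounded, both versions support about 5%, 7%, 12% and 20%. At 10% overlap the two-sided rate is essentially nominal. The rate in the RLI-worse direction is 4.3% against a nominal 2.5%.

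**Step 4: cost of relying on new children only.** If the total stays at 54 per group, the new-only sample is 54(1 − f) per group. Its power for 2.53 degrees is Φ(2.53/(3.981√(2/(54(1 − f)))) − 1.96). This gives 91% at no overlap and 88%, 84%, 79% and 73% at 10%, 20%, 30% and 40%.

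**The case against.** The strongest reply is that nothing in the article says any earlier child enters Part 1. Recruitment dates and source records are details that a condensed article may leave to the full protocol, and the Part 1 flow diagram is not shown. This stands as far as the size of the problem goes. A reader might infer that the finding is in fact being retested on its own data, but the documents show only that the rules permit it. The eligibility lists are, however, printed as numbered lists, and as written they admit these children.

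Second, the rules may remove some of them. Exclusion item 2 takes out children re-operated for residual dysplasia, and the Introduction mentions residual limbus seen during such surgery. The 5-year rule may remove others: the Abstract calls the earlier follow-up short-term, although the Introduction calls the MRI series long-term. This stands, and it makes full carry-over of 2.53 degrees an upper-end assumption.

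Third, a reader might infer that the earlier children were picked because they showed the effect. The documents do not support that. The Introduction describes a prospective follow-up series, and it was the cohort as a whole that raised the hypothesis.

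Fourth, a reader might infer that the 32.2% cut-off is tested in a circle. Section 2.2.1.4 states no test of 32.2%; it re-estimates a cut-off. The risk is agreement that flatters the old value, not a circular test.

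Fifth, following the same children for longer serves the long-term aim in 2.1 and answers the limitations given in the Discussion. This stands, and it argues against a blanket exclusion. It does not argue against keeping the confirmatory claim separate.

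Finally, Part 1 as described does not require serial MRI. Initial inversion is measured by arthrography and residual status by MRI at follow-up. The imaging argument therefore makes overlap plausible and does not show that it is large.

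**Conclusion.** The concern holds in a conditional form. Part 1 has verification among its purposes, and its eligibility rules do not secure independence from the cohort that raised the hypothesis. The RLI comparison and the re-estimated cut-off may therefore rest partly on the original data.

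The size depends on an overlap that the documents do not give. At 10% it is negligible for the two-sided error rate. At 20% to 40% the false-positive rate is about 7% to 20%, with a shift of 0.51 to 1.01 degrees. These figures assume equal overlap in both groups, full persistence of the published 2.53 degrees in carried-over children, no difference in new children, and 54 evaluable per group. The earlier cohort is described as small and Part 1 is multicenter, so low overlap is quite possible. The effect on the cut-off cannot be quantified from the documents, but its direction is towards the old value, and that value is used in parts 2 and 3.

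The sample size itself is correct.

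**What to change.** In 2.2.1.4, add that:

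1. each child is flagged for membership of the team's earlier published cohorts, and the number is reported by group and center;
2. the confirmatory acetabular-index comparison, and the check of the ROC cut-off (its sensitivity and specificity), use only children who were not in those cohorts;
3. the pooled analysis and the extended follow-up of the earlier children are reported alongside as supportive.

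This keeps the long follow-up of the earlier children in the study. It costs a flag in the database and a few sentences in the plan. The downside is lower precision in the confirmatory set if overlap is material: at an unchanged total, power falls from 91% to about 84% at 20% overlap. Applying the target of 67 per group to children outside the earlier cohorts would avoid that loss, at the price of finding more eligible children at the other centers.
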